## Abstract

**Background:**

The autonomic nervous system plays a vital role in regulating physiological functions. Transcutaneous auricular vagus nerve stimulation (taVNS) is a method that provides insights into autonomic nerve modulation. This paper presents a research protocol investigating proof of mechanism for the impact of taVNS on autonomic functions and aims to both deepen theoretical understanding and pave the way for clinically relevant applications.

**Methods:**

This protocol employs a single-blind, randomized cross-over design involving 10 healthy male participants. Simultaneous assessment of both the afferent and efferent aspects of the vagus nerve will be performed by integrating physiological measures, magnetic resonance imaging, and a questionnaire survey. Electrocardiogram will be measured to assess changes in heart rate, as a primary outcome, and heart rate variability. Active taVNS and sham stimulation will be compared, which ensures precision and blinding. Electrical stimulation will be applied to the left *concha cymba* and the left *lobule* for the active and sham conditions, respectively. The specific parameters of taVNS involve a pulse width of 250 µs, a frequency of 25 Hz, and a current adjusted to the perception threshold (0.1 mA ≤ 5 mA), delivered in cycles of 32 s on and 28 s off.

**Conclusions:**

This research investigates proof of mechanism for taVNS to elucidate its modulatory effects on the central and peripheral components of the autonomic nervous system. Beyond theoretical insights, the findings will provide a foundation for designing targeted neuromodulation strategies, potentially benefiting diverse patient populations experiencing autonomic dysregulation. By elucidating the neural mechanisms, this study contributes to the evolution of personalized and effective clinical interventions in the field of neuromodulation.

**Trial Registration:**

JRCT, jRCTs032220332, Registered 13 September 2022; https://jrct.niph.go.jp/latest-detail/jRCTs032220332.

## Background

The autonomic nervous system (ANS) plays an indispensable role in various physiological functions, including cardiovascular activity, visceral perception, and emotional states [1]. Maintaining homeostasis relies on the delicate balance between the sympathetic and parasympathetic branches of the ANS [2]. Transcutaneous auricular vagus nerve stimulation (taVNS) has emerged as a cutting-edge tool to elucidate the mechanisms of autonomic regulation [3]. As a linchpin of the parasympathetic system, the vagus nerve’s extensive connections with the central nervous system positions it at the core of autonomic control [4]. Recent advancements underscore the potential of taVNS to modulate autonomic activity and influence functions such as heart rate and heart rate variability (HRV) [5, 6]. To gain a more comprehensive understanding, it is imperative to integrate these validated insights by examining indices of the afferent (e.g., brain magnetic resonance imaging [MRI]) and efferent (e.g., heart rate, pupil diameter) branches.

Offering a non-invasive approach with therapeutic potential, taVNS holds promise for addressing autonomic dysregulation [3]. The present study employs a comprehensive approach that integrates physiological, neural, and perceptual assessments to unravel the intricate influence of taVNS on autonomic functions, bridging the gap between theoretical understanding and clinical application. The study aims to investigate the proof of mechanism (POM) behind taVNS, focusing specifically on heart rate as a primary outcome and HRV and brain MRI as key indicators of vagal influence on the efferent and afferent tracts, respectively. Building on prior findings, this study investigates the immediate effects of taVNS intervention on autonomic functions through the use of a stimulus variable known for heart rate modulation.

This comprehensive assessment includes physiological measures, functional MRI (fMRI), and perceptual evaluations and provides a nuanced understanding of the impact of taVNS on autonomic pathways. fMRI is a reliable and complementary physiological assessment of afferent response, and by exploring changes in brain connectivity, it sheds light on the neural underpinnings of taVNS [7] by providing a reliable index to investigate the effects of taVNS modulation through the afferent branch. This holistic approach positions our study at the forefront of research and aims to establish a solid measurement of parasympathetic response though vagus nerve stimulation. Specifically, we seek to elucidate the association between the vagus nerve and autonomic functions, which has valuable implications for clinical applications and advancing our understanding of the neural mechanisms underlying autonomic regulation.

A previous study reported significant reductions in heart rate following taVNS stimulation in 15 healthy participants [5]. In another study, changes in HRV were observed in 13 healthy participants [6]. However, these changes were transient, lasting only 30–60 s, and thus lacked sustained effects. Notably, these studies used mixed-gender data, employed various stimulus variables, and were designed to assess the strength of effects on heart rate. Robust short-term decreases in heart rate and alterations in HRV immediately post-stimulation were consistently observed across all stimulus variables.

In the present study, we aim to enhance the specificity of our investigation by adopting a stimulus variable known to induce a more potent effect on heart rate reduction (25 Hz). Focusing on the short-term effects as the primary evaluation criterion, we anticipate detecting a reduction in heart rate in 10 cases by focusing on male subjects to exclude the effect of differences by sex. Because empirical evidence has demonstrated the impact of the menstrual cycle on the vagal nerve system [8, 9], this strategic approach of restricting the participants to men allows for a more nuanced understanding of the immediate impact of taVNS on heart rate dynamics by controlling the potentials that confounds such effects. Therefore, in this study, we will conduct a sham-controlled, single-blind randomized controlled trial targeting a healthy population, with the aim of pinpointing the POM for taVNS. The adoption of a single-blind study design ensures that participants remain unaware of whether they are receiving actual taVNS stimulation or a placebo intervention. This rigorous methodology was chosen to provide a thorough insight into the mechanisms underlying the effects of taVNS in a healthy population.

## Methods

### Participants

Ten healthy male participants will be recruited via internal advertisement at the institute where the research is to take place. The inclusion criteria include healthy males aged 20–39 years. Exclusion criteria are smokers, individuals with regular medication intake, a history of glaucoma or cerebrospinal fluid shunt surgery, and auricular hematoma (to facilitate the placement of taVNS electrodes). Participants will also be screened for MRI exclusion criteria, including nonremovable metal parts in/on the body, tattoos, known neurological diseases, and claustrophobia. Eligibility and exclusion criteria will be assessed through a physician interview. Participants deemed eligible have already been approached for written consent.

### Procedures

#### Experimental design

A single-blind randomized cross-over design will be used. Random assignment will be performed using a computer-generated randomization system by an institutional Academic Research Organization section to determine whether the participants would be assigned to the target or sham session first.

#### Baseline assessment (pre)

The participants will undergo baseline assessments before the stimulation phase: will include a self-report questionnaire, MRI (40 min), and measurement of physiological parameters: electrocardiogram (ECG); pupil diameter, 15 min; heartbeat perception task, 5 min.

#### Stimulation phase

Physiological parameters (ECG; pupil diameter. 15 min; heartbeat perception task. 5 min) will be measured under stimulation. MRI (rest, 15 min) will also be performed during stimulation.

#### Post-stimulation assessment

The assessment will continue without stimulation. Physiological parameters (ECG; pupil diameter, 15 min; and heartbeat perception task, 5 min) will be measured, MRI (rest, 15 min) will be performed, and a self-report questionnaire will be administered.

#### Cross-over evaluations

The same set of evaluations will be conducted at intervals of at least 1 week (details shown in the *Interval Considerations* section below). Stimulation methods will be crossed to account for any variations.

#### Adverse event evaluation

Participants will be instructed via email to contact the physician if they experience any adverse events during the experimental period (from the first test date to 1 week after the second test date).

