#### Somatic symptom scale-8 (SSS-8)

The SSS-8 was designed to assess the physical symptoms of study participants. This self-report questionnaire consists of 8 items and assesses somatic symptom burden. It uses a five-point Likert scale, with higher scores indicating higher levels of somatic symptoms [18]. The current study will use the Japanese version of the SSS-8, which has been validated linguistically and psychologically and has been shown to have good internal consistency [19].

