##### Stimulus variables

Pulse width: 250 µs, Frequency: 25 Hz, Current: perception threshold (0.1 mA ≤ 5 mA), 32 s on/28 s off.

Utilizing the stimulus variables of the tVNS®L medical device, a 15-min duration allows for a thorough examination of the effects of taVNS with minimal burden on the participant. The frequency of taVNS will be set to below the participants’ pain perception in both the target and sham stimulation trials.

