#### Behavioral and psychological measures

The relation between the rate of change in internal perception, physical symptoms, and psychiatric symptom scale as well as the rate of change during taVNS and sham stimulation will be evaluated using analysis of variance and statistical modeling.

To this end, the MAIA, STAI, and SSS-8 will be analyzed by performing a *t*-test for each total score and sub-score, by comparing taVNS and sham sessions. Additional analyses will also be performed when deemed necessary or significant.

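### The only adverse event route described is participant-initiated contact after an e-mail instruction, so mild events may be missed and enquiry is not the same after taVNS and sham

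*Protocol article*

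**What the plan says.** The Adverse event evaluation section under Procedures is one sentence: "Participants will be instructed via email to contact the physician if they experience any adverse events during the experimental period". The period is defined as "from the first test date to 1 week after the second test date". The participant starts the report, the trigger is his own judgement that something is an adverse event, and one rule covers both test days and the time between and after them.

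The Abstract describes a "single-blind, randomized cross-over design involving 10 healthy male participants". Each man therefore attends for one active and one sham session, at least 1 week apart (Cross-over evaluations; Interval considerations).

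Other sections touch on symptoms but not on adverse event recording:

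- Post-stimulation assessment ends with a questionnaire: "and a self-report questionnaire will be administered". The instrument is not named there.
- Among the instruments, "The SSS-8 was designed to assess the physical symptoms of study participants".
- Under Behavioral and psychological measures, "the MAIA, STAI, and SSS-8 will be analyzed by performing a *t*-test for each total score and sub-score", comparing the taVNS and sham sessions.
- Under Stimulus variables, the stimulation (the sentence says frequency) "will be set to below the participants’ pain perception in both the target and sham stimulation trials".

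**The concern.** Spontaneous reporting depends on the participant deciding that a symptom is worth a message to a physician. Tingling or skin irritation at the electrode is the sort of event least likely to prompt one. Because stimulation is to be kept below pain perception, mild events are also the kind most plausibly expected.

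The cross-over adds a second weakness. Each man is seen after both conditions, so identical questions after each session would give a within-person record of tolerability at almost no cost. Under spontaneous contact there is no fixed occasion of enquiry, so a report after one session and silence after the other may reflect a difference in events or only a difference in the impulse to write.

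The Discussion presents the work as a foundation for clinical trials in patients. A later statement that no adverse events occurred would carry little weight if it could equally mean that nobody made contact.

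**Working it through.** **Text check.** The article states no adverse event rate, reporting rate or safety endpoint, so there is no figure to reproduce. The question is whether any section supplies an active enquiry.

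| Section | What it provides | Active adverse event enquiry? |
|---|---|---|
| Adverse event evaluation | E-mail instruction to contact the physician | No; the participant initiates |
| Baseline assessment; Post-stimulation assessment | Self-report questionnaire before and after stimulation | Not described as such |
| Somatic symptom scale-8 | Eight items on general somatic burden | No stated link to adverse events |
| Behavioral and psychological measures | *t*-tests on total scores and sub-scores | No; analysed as outcomes |
| Stimulus variables | Level kept below pain perception | Implies asking about sensation at set-up, not about events |

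No section describes a scheduled adverse event question or checklist.

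**Illustration of how much could be lost.** Every rate here is an assumption; only n = 10 is from the article. Let p be the chance that a man has a mild event and r the chance that an affected man makes contact. With independent men, a given man has a recorded event with probability p × r, so

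P(at least one recorded) = 1 − (1 − p × r)^10, and expected men with a recorded event = 10 × p × r.

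| p | r = 1 | r = 0.75 | r = 0.50 | r = 0.25 |
|---|---|---|---|---|
| 10% | 0.651 | 0.541 | 0.401 | 0.224 |
| 20% | 0.893 | 0.803 | 0.651 | 0.401 |
| 30% | 0.972 | 0.922 | 0.803 | 0.541 |

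For p = 20% and r = 0.50: 1 − (1 − 0.10)^10 = 1 − 0.349 = 0.651, with 10 × 0.10 = 1.0 man expected on record instead of 2.0.

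**A second view.** Suppose exactly 3 of the 10 have a mild event (also assumed). The chance that none is recorded is (1 − r)^3:

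- r = 0.3: 0.7^3 = 0.343
- r = 0.5: 0.5^3 = 0.125
- r = 0.7: 0.3^3 = 0.027

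The result runs from about one in three to under 3% depending on r alone. Each man missed is 1/10, or 10 percentage points, of the recorded proportion.

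**The case against.** The strongest reply is that this is one sentence in a condensed article. It sets out an instruction to participants and does not say that staff will refrain from asking. End-of-session questions and event forms are commonly left to the full protocol, which is not shown. This stands in part: a reader might infer that spontaneous contact is the sole route in the trial, but the article supports only that it is the sole route described. It does not remove the point, because the article gives a method under its own heading, and that method is passive.

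Four further inferences are tempting and are not supported:

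- *Mild events will be under-recorded.* Without a reporting rate, the most that can be said is that they may be. At an assumed r of 0.7, the chance of recording none of three events is only 2.7%.
- *An event cannot be tied to taVNS or sham.* It can. The sessions are at least 1 week apart, the randomised order is known to an experimenter, and a dated report can be matched to the session before it.
- *A planned tolerability comparison is lost.* None is planned. The aim is proof of mechanism, with heart rate as the primary outcome.
- *No symptoms are solicited at all.* A questionnaire is given before and after stimulation, and it may include the SSS-8. Some self-report of physical symptoms by condition is therefore possible, but it is a general scale and is not described as feeding adverse event records.

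A practical objection also stands. Under Device application the participant is covered at once so that other experimenters cannot see the allocation. A routine inspection of the ear could reveal concha or lobule to a blinded evaluator.

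**Conclusion.** The point holds in a limited form. The described method is participant-initiated; it may miss mild events, and it does not provide fixed, equal enquiry after the two conditions. The size of the loss is unknown, and the tables above show only how strongly it depends on assumed rates. The primary heart rate comparison does not depend on adverse event reports and is unaffected.

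It is still worth acting on. The remedy uses contacts that already exist, and information not asked for at a session cannot be fully recovered later. If the full protocol already has active questioning, stating so in the article settles the matter.

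**What to change.** Put the same open question on adverse events to every participant:

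1. at the end of each session;
2. at the start of session 2, covering the time since session 1;
3. by an e-mail that requests a reply, 1 week after session 2.

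Record each answer, including a negative one, against its session, and tabulate by taVNS and sham. Keep the spontaneous-contact route for events between these points. If the electrode site is checked, only the experimenter who already knows the allocation should do it, so that evaluator blinding is kept.

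The cost is a few minutes per session and one e-mail per man. The downside is that a few more trivial events will be recorded.

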#### Interval considerations

An interval of at least 1 week will be maintained to eliminate the potential carryover effect of taVNS (15-min stimulation). Previous studies employing crossover designs have utilized various stimulus intervals, including 50-min stimulation, 48-h interval [10]; 4-min stimulation, 1-week interval [11]; and 30-min stimulation, 1-week interval [12]. Based on the fact that prior studies set a maximum of 1 week to eliminate the carryover effect, we also set a 1-week interval in the present study, thereby aligning with previous practices.

### Heartbeat perception task

To examine the effects of the taVNS on changes in visceral perception, we will employ a heartbeat detection task. Participants will be instructed to independently count their heartbeats during specific intervals (25 s, 35 s, and 45 s) without relying on palpation, while their actual heart rate was concurrently monitored using a pulse meter (see [13] for details).

### Physiological measures

#### ECG

ECG will be measured using a two-lead ECG acquisition device (BrainAmp; Brain Products GmbH, Gilching, Germany) in order to assess changes in heart rate, as a primary outcome, and HRV. ECG data will be recorded using two disposable sticker-type electrodes, one on the left arm and one on the right arm, and another electrode on the right leg.

#### Pupil diameter

The variation in pupil diameter may reflect the activity of the nucleus tractus solitarius and the nucleus accumbens. Therefore, we will seek to evaluate the POM for the taVNS by analyzing the rate of change before and after stimulation. Pupil diameter was measured using a wearable eye-tracking device (Pupil Core; Pupil Labs, Berlin, Germany).

#### MRI acquisition

An MRI system equipped with a head coil (MAGNETOM Skyrafit 3T; Siemens Healthineers, Erlangen, Germany) will be used to acquire an anatomical volume image and fMRI images of each participant. To obtain a reference image for analysis, a structural image (T1-weighted magnetization-prepared rapid gradient-echo) will be captured with the following sequence parameters: repetition time (T_R_)/echo time (T_E_) = 2500/2.18 ms, voxel size = 0.8 × 0.8 × 0.8 mm, flip angle = 8°, and field of view (FOV) = 206 × 206 mm. To obtain resting-state fMRI images, parameters for single-shot echo-planar imaging will be set at T_R_/T_E_ = 800/34.4 ms, 60 axial slices with a thickness of 2.4 mm and a 0.6-mm interslice gap, flip angle = 52°, matrix size = 86 × 86, and FOV = 206 × 206 mm. Images will be angled along a line connecting the anterior and posterior commissures.

Our protocol aligns with the harmonized protocol for clinical MRI studies in the context of a national project, Brain/MINDS Beyond (https://brainminds-beyond.jp) to ensure standardized and high-quality neuroimaging. During resting-state fMRI, participants will be asked to keep their eyes open in order to ensure consistent data collection.

### Questionnaires

#### Multidimensional assessment of awareness of interoceptive awareness (MAIA)

The MAIA was designed to examine the interoceptive-perceptive characteristics of study participants. This self-report questionnaire consists of 32 items and assesses 8 dimensions of trait interoceptive sensitivity [13]. The current study will use the Japanese version of MAIA, which has been validated using exploratory factor analyses that resulted to reducing the questionnaire items from 32 to 25 and from 8 to 6 dimensions [14]. Despite these modifications, the items used in the current study will include the original 32-item version to ensure compatibility with data from previous research [15].

#### State-trait anxiety inventory (STAI)

The STAI was designed to examine mood changes in individuals undergoing taVNS. This self-report questionnaire consists of 40 items and measures state anxiety and trait anxiety. It uses a four-point Likert scale, with higher scores indicating greater anxiety [16]. The Japanese version of STAI will be used in the current study. Its reliability and validity have been confirmed [17].

#### Somatic symptom scale-8 (SSS-8)

The SSS-8 was designed to assess the physical symptoms of study participants. This self-report questionnaire consists of 8 items and assesses somatic symptom burden. It uses a five-point Likert scale, with higher scores indicating higher levels of somatic symptoms [18]. The current study will use the Japanese version of the SSS-8, which has been validated linguistically and psychologically and has been shown to have good internal consistency [19].

### Interventions

#### Active taVNS

Active taVNS will be performed using a tVNS®R stimulator (tVNS Technologies GmbH, Erlangen, Germany), an adaptation of the commercially available tVNS®L medical device in Europe tailored for clinical research with adjustable stimulation variables. tVNS®R is considered a medical device in Europe, which is pivotal in our study.

#### Stimulation protocols

##### Test Stimulation (taVNS stimulation)

Electrical stimulation will be applied to the left auriculovagal boat (an area innervated by the auricular vagus nerve).

##### Control stimulus (Sham Stimulation)

Electrical stimulation will be applied to the left *lobule*.

##### Stimulus variables

Pulse width: 250 µs, Frequency: 25 Hz, Current: perception threshold (0.1 mA ≤ 5 mA), 32 s on/28 s off.

Utilizing the stimulus variables of the tVNS®L medical device, a 15-min duration allows for a thorough examination of the effects of taVNS with minimal burden on the participant. The frequency of taVNS will be set to below the participants’ pain perception in both the target and sham stimulation trials.

##### Device application

An experimenter with knowledge of the allocation results will affix the electrodes to the participant’s auricular region just before the baseline examinations and the heartbeat perception task. Immediate covering of the participant ensures evaluator blinding, preventing other experimenters from observing the allocation results. This approach ensures precision in stimulation, control, and blinding, thereby maintaining the integrity of the study’s findings.

